#### Safety outcomes

2.10.3

The abnormal of vital signs, blood examination, urine examination, liver and kidney function, fecal occult blood, coagulation function and electrocardiogram are recorded in detail and comprehensively analyzed. If they are related to drugs, we will immediately stop using the drug.

#### Adverse event reporting

2.10.4

Adverse reaction (AE) refers to the occurrence of adverse reactions that are not related to the purpose of treatment in the process of preventing, diagnosing, or treating diseases according to normal usage and dosage. The AE is decided by the clinical expert from the coordination center. The time of onset, clinical manifestations, possible related drugs, solutions, and outcomes should be recorded.

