**Method::**

For this prospective cohort study, we will enroll 300 COVID-19 patients aged 18 to 80 years at 4 centers. We divide them into 2 groups, according to whether they use *Baidu Jieduan Granule* at a ratio of 1:1. We will compare treatments combined *Baidu Jieduan Granule* with conventional Western medicine (experimental group) vs treatment of conventional Western medicine only (control group). The basic information of patients including demographic, general condition, primary diseases, and complications will be assessed. Related examines will be conducted at 1, 3, 5, 7, and 14 days. The primary outcomes are clinical outcome. A follow-up time of 1 year (to June 30, 2021) allow us to evaluate the psychiatric disorder after recovery. We will monitor adverse events throughout the trial.

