“Internal and External Relieving -Truncated Torsion” strategy means in the very beginning of COVID-19, we use TCM which can release the exterior (sweating) or dredging the interior (draining and defecating) to intervene timely so that we can remove pathogenic factors, treat diseases and then prevent common type COVID-19 patients from developing into severe and critical illnesses. This theory originates from the idea of “ preventive treatment of disease” in “ *Inner Canon of Yellow Emperor*”. In the long-term struggling against hundreds of thousands of times of infectious disease outbreak, this theory gradually got improved and perfected. Wu Youke, the most famous expert of contagious disease in Ming Dynasty, proposed that the pathogenic factors should be eliminated as soon as possible in his book “*Plague Theory*”.^[10]^ Ye Tianshi, another great medical expert, also put forward the viewpoint of protecting the organs which are not attacked first in “*Treatise on Epidemic Febrile Diseases*”.^[11]^

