The main components of *Baidu Jieduan Granule* are *Cmnamomi Mmulus* which can promote sweating, *Radix Rhei Et Rhizome* and *Gypsum Fibrosum* both of which can dredge the interior. We also add some other components with heat-clearing and antiviral effects considering the features of COVID-19. Among them, *Cmnamomi Mmulus*, *Radix Rhei Et Rhizome* and *Gypsum Fibrosum* have shown sound clinical results in the treatment of viral and bacterial pneumonia for more than 10 years.^[12,13]^ Since January 2020, *Baidu Jieduan Granule* has been applying in hospitals in Wuhan and other epidemic areas in Hubei province to cure COVID-19 or some suspicious patients with respiratory infection symptoms. Combining the data from these studies and data from previous, it demonstrated that *Baidu Jieduan Granule* is of great effects and high safety. Moreover, modern pharmacological studies have proved that *Radix Rhei Et Rhizome* has the function of antibacterial and antivirus, for example, streptococcus A, streptococcus B, Streptococcus pneumonia, staphylococcus aureus, influenza virus A and influenza virus B. It can also significantly reduce the levels of TNF-α, IL-2, IL-6, IL-8 and other inflammatory cytokines in patients with systemic inflammatory response syndrome (SIRS), inhibit the excessive inflammatory reaction and maintain immune stability.^[14]^ In primary studies, *Cmnamomi Mmulus* plays an immunosuppressive role by inhibiting the proliferation of spleen cells.^[15]^ Cinnamyl alcohol can alleviate airway and lung inflammation by reducing the release of inflammatory factors and cytokines.^[16]^*Gypsum Fibrosum* is composed of 2 layers of silica tetrahedron and 1 layer of magnesium oxide octahedron.^[17]^ The surface adsorption capacity and electrostatic adsorption capacity of *Gypsum Fibrosum* can fix the virus and its toxin on the mucosal surface of the small intestine, making it lose the ability to cause disease.^[18,19]^

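### Section 2.10.4 defines an adverse event as a drug reaction, so non-serious symptomatic events may be under-counted, possibly unequally between the groups

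*Protocol article*

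**What the plan says.** The Abstract (Method) commits the study to events in general: "We will monitor adverse events throughout the trial". Table 1 in section 2.14 has a row for recording adverse events at every node from D1 to D14. Section 2.2 makes safety part of the main aim.

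Section 2.10.4 then gives the working definition: "Adverse reaction (AE) refers to the occurrence of adverse reactions that are not related to the purpose of treatment", and limits it to reactions arising "in the process of preventing, diagnosing, or treating diseases according to normal usage and dosage". Who applies it is stated: "The AE is decided by the clinical expert from the coordination center". For each accepted event the article asks for these details: "The time of onset, clinical manifestations, possible related drugs, solutions, and outcomes should be recorded".

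Section 2.10.3 is a separate safety list. It covers abnormal vital signs, blood and urine tests, liver and kidney function and fecal occult blood, and ends: "coagulation function and electrocardiogram are recorded in detail and comprehensively analyzed".

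The Introduction describes the treatment strategy as one that can "release the exterior (sweating) or dredging the interior (draining and defecating". It credits one component of the granule as one "which can promote sweating" and two others with acting on the interior.

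**The concern.** An adverse event is normally any untoward occurrence, and causality is judged afterwards. An adverse reaction is the subset attributed to a drug. Section 2.10.4 uses the abbreviation for the first with the meaning of the second, so a causality judgement decides what is counted at all. A symptom put down to COVID-19, or to no drug, does not meet the definition as written. The further condition about the purpose of treatment leaves room to set aside effects regarded as part of the granule's action.

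This matters because safety is a main aim and only one group takes the granule (2.9). If the filter lets through different shares of events in the two groups, a comparison of AE rates reflects attribution as well as harm.

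**Working it through.** The article states no AE rate and no safety sample size, so there is no figure to reproduce. The check sets the sections side by side.

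1. **Is the definition at odds with the rest of the article?** Yes. The heading of 2.10.4, the Abstract and Table 1 all speak of events. The definition speaks of reactions, with limits on purpose and dosage.

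2. **What is captured elsewhere, whatever its cause?**
   - Rapid breathing, desaturation, shock, respiratory failure, organ failure and death are components of worsening in the primary outcome (2.10.1).
   - Abnormal vital signs, laboratory tests, fecal occult blood and ECG are recorded under 2.10.3. Relatedness there affects only continuation of the drug, not recording.
   - Section 2.6 lists serious adverse events as a reason for withdrawal and sets no relatedness condition. It is a withdrawal rule rather than a recording rule, but it suggests that serious events are noticed.

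3. **What remains?** Non-serious symptoms such as diarrhoea, vomiting, sweating and rash. None is on the 2.10.3 list or among the criteria for worsening. The only stated route for them is the 2.10.4 definition.

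4. **How could such an event fail the definition?**
   - (a) The expert attributes it to COVID-19 or to no drug, so it is not a reaction.
   - (b) The expert regards a bowel or sweating effect as part of the granule's intended action. The Introduction makes this possible, but no section says it will be done.

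5. **What would this do to the comparison?** As a simplification, count at most one event per patient. Let p be the true event rate in a group and c the share of events accepted as AEs, with E for the experimental and C for the control group. Then

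   observed rate = p × c

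   observed rate ratio = (p_E / p_C) × (c_E / c_C)

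   observed rate difference = p_E c_E − p_C c_C

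   - If c_E = c_C < 1, the ratio is preserved, but the counts and the rate difference shrink.
   - If c_E < c_C, as under route (b), the granule looks safer than it is.
   - If c_E > c_C, for example because symptoms in patients on a new product are more readily ascribed to it, the granule looks worse than it is.

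6. **Can c_E and c_C differ?** Granule use defines the groups (2.8) and no masking is described, so nothing stated prevents it. The article does not say whether the deciding expert knows the group.

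7. **Can the effect be sized?** No. None of p_E, p_C, c_E and c_C is given in the article. Any power or false-positive figure would rest wholly on chosen values, so none is offered.

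**The case against.** The strongest reply is that little is lost. The Introduction presents sweating and draining as means. The aims it names are removing pathogenic factors, treating disease and preventing progression. The definition excludes reactions tied to the purpose, not to the mechanism, so harmful diarrhoea or heavy sweating could still be counted. Deterioration, death and test abnormalities are captured elsewhere. The decision rests with the coordination center, whose experts come from other hospitals and universities (2.1). Asking for possibly related drugs suggests a loose causality standard. The case report form (Additional file 5) is not shown and may collect more.

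Much of this stands. A reader might infer that all unattributed events drop out, that the granule's bowel and sweating effects are lost altogether, or that the safety comparison is shown to be biased. The documents support none of these. Sections 2.10.1 and 2.10.3 capture a great deal irrespective of cause, no text says that intended effects will be excluded, and bias is a risk rather than a result.

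Three things in the reply do not remove the point. The field for possibly related drugs is filled in for events already accepted as AEs, so it does not widen the definition. No written rule requires the expert to count a harmful excess of an intended effect. And whatever the form collects, the published rule for what counts as an AE is the narrower one.

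**Conclusion.** The point holds in a limited form. Section 2.10.4 labels an adverse-reaction definition as AE and contradicts its heading, the Abstract and Table 1. If it is followed as written, non-serious symptomatic events may be under-counted, and possibly to a different extent in the two groups.

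The size cannot be derived from the article. If effects seen as intended are excluded, the direction favours the granule. For unattributed events the direction is open, since it depends on how events are attributed in each group.

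This rests on two assumptions: that the definition is applied literally, and that no further instruction in the unseen case report form overrides it. Confidence is therefore medium. The correction should be made because safety is a main aim and the change is simple.

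**What to change.** - In 2.10.4, define an AE as any untoward medical occurrence in either group from D1, whether or not drug-related and whether or not linked to an intended effect of treatment.
- Record relatedness as a separate field that plays no part in deciding whether an event is counted.
- Make the comparison of all-cause AEs and SAEs between groups the main safety analysis, with drug-related events in a secondary table.
- Section 4.1 places the study in its follow-up phase. For patients already treated, recode the existing case report forms and records by the same rule in both groups, as far as they allow, and report where symptoms were not recorded.

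The cost is a wording change, the recoding work, and higher reported AE counts. Symptoms never written down cannot be recovered, and the report should say so.

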#### Mental health outcomes

2.10.5

In our study we evaluate psychiatric disorder symptoms of patients with Liebowitz Social Anxiety Scale (LSAs, Additional file 3) and Depression, Anxiety and Stress Scale (DASS21, Additional file 4). LASs measure assesses the way that social phobia plays a role in our life across a variety of situations. There are 24 items in LSAs, each item has 2 questions, the first question asks how anxious or fearful you feel in the situation (0=None, 1=Mild, 2=Moderate, 4=Severe), the second question asks how often you avoid the situation (0=Never, 1=Occasionally, 2=Often, 3=Usually). The final score 55–65 means moderate social phobia, 65–80 marked social phobia, 80–95 severe social phobia, greater than 95 very severe social phobia. DASS21 is a 21 question assessment that was developed to measure the degree of depression, anxiety and stress in an individual. It includes 7 questions for each and the scores are calculated by adding up the scores for each item in the section. There are 5 rating (Normal, Mild, Moderate, Severe, Extremely Severe) of each section according to the score.

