In this multicenter, prospective cohort study, we aim to use the *Baidu Jieduan Granule* combined with Western medicine to dynamically observe the changes of patient's blood, cytokines, coagulation function, chest computed tomography (CT), respiratory distress (respiratory rate, RR), blood oxygen saturation, oxygenation index, and patient prognosis (healing, worsening, and death),to prove the clinical efficacy of *Baidu Jieduan Granule* in curing COVID-19, to reveal the possible mechanism from the immune route, and to evaluate the safety. We will also assess mental health outcomes through our 1 year follow-up.

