#### Primary outcomes

2.10.1

The primary outcomes of our study are clinical outcomes. In our study, there are 4 kinds of clinical outcomes:

1.recovery, the following conditions shall be met:1.the body temperature is normal for 3 consecutive days2.respiratory symptoms disappeared completely,3.the nucleic acid test of respiratory tract samples is negative for 2 consecutive times (the sampling interval is at least 1 day);2.condition improved, meet any of the following 2 items:1.the clinical symptoms are significantly relieved,2.the nucleic acid of sputum, nasopharynx test paper and other respiratory tract samples are negative for 2 consecutive times (the sampling interval should be at least 24 hours);3.condition worsen, one of the following situations occurs:1.shortness of breath, respiratory rate (RR) ≥30 times/minutes,2.oxygen saturation ≤93% in resting state,3.arterial oxygen partial pressure (PaO2) / fraction of inspired oxygen (FiO2) ≤300 mm Hg,4.shock,5.respiratory failure, requiring ventilator support,6.organ failure needing intensive care, and7.death.

We count the number of patients of each kind of clinical outcomes then calculate the ratio.

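### The social anxiety scale's fear code (0, 1, 2, 4) does not match its avoidance code (0–3), and scores of 65 and 80 each fall in two severity bands

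*Protocol article*

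**What the plan says.** Section 2.10.5 (Mental health outcomes) describes the scale and how it is scored. "There are 24 items in LSAs, each item has 2 questions". The first question, on fear or anxiety, is coded "0=None, 1=Mild, 2=Moderate, 4=Severe". The second, on avoidance, is coded "0=Never, 1=Occasionally, 2=Often, 3=Usually". The total is then classified: "The final score 55–65 means moderate social phobia, 65–80 marked social phobia, 80–95 severe social phobia, greater than 95 very severe social phobia". For the instrument itself the section points to an attachment, "Liebowitz Social Anxiety Scale (LSAs, Additional file 3", which is not among the documents at hand.

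On the outcome's role, section 2.10.1 states: "The primary outcomes of our study are clinical outcomes". The scale is therefore not primary. Mental health is nevertheless part of the aim in section 2.2, and the Introduction says: "We will also assess mental health outcomes through our 1 year follow-up". Table 1 places this scale and the depression, anxiety and stress scale in the follow-up phase. They are the only two mental health instruments named. The published Correction changes a date only, so the scoring text stands as printed.

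**The concern.** Both questions offer four ordered answers on the same items, yet only the fear code skips a number. Under the printed code, the step from Moderate to Severe fear counts two points and every other step counts one. The article gives no reason for this. If the 4 is a slip and data are scored from the article, totals rise for patients who report severe fear, while the cut-offs do not move.

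The second defect is independent of the first. Adjoining bands share an end point, so the rule does not give every score a single class.

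At stake are the level and spread of the total score and, if classes are tabulated, the class counts, for one of the two scales that carry the long-term mental health aim.

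**Working it through.** The article states no maximum total, so there is no printed figure to reproduce. The check is direct arithmetic.

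**Inputs (all from section 2.10.5)**
- Items: 24, with two questions each.
- Fear code: 0, 1, 2, 4. Avoidance code: 0, 1, 2, 3.
- Bands: 55–65 moderate, 65–80 marked, 80–95 severe, above 95 very severe.
- Assumption 1: the final score is the sum of all 48 answers (24 × 2). The article does not spell this out.
- Assumption 2: the intended code for Severe fear is 3, as for the top avoidance answer.

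**Maximum total**
- As printed: 24 × 4 + 24 × 3 = 96 + 72 = 168.
- With fear coded 0–3: 24 × 3 + 24 × 3 = 72 + 72 = 144.
- Difference: 168 − 144 = 24.

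**Surplus for one patient**
- Let k be the number of fear items answered Severe. Surplus = k × (4 − 3) = k, so it runs from 0 to 24.
- A patient with no Severe fear answer has no surplus, however high the avoidance score.

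**Effect on class.** The three closed bands span 10, 15 and 15 points. What matters is the distance to the next cut-off:

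| Total with fear 0–3 | Severe fear answers | Total as printed | Change |
|---|---|---|---|
| 54 | 1 | 55 | no band → moderate |
| 60 | 5 | 65 | moderate → shared score (moderate or marked) |
| 70 | 10 | 80 | marked → shared score (marked or severe) |
| 85 | 11 | 96 | severe → very severe |
| 95 | 1 | 96 | severe → very severe |

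One further Severe answer takes the second and third rows clearly into the higher class (66 and 81).

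**Effect on a group comparison.** Each group's mean rises by that group's mean of k. The difference in means therefore changes by mean k (experimental) − mean k (control). This is zero if the groups report severe fear equally often.

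**Overlap of bands.** Checking every integer from 0 to 168 against the bands, read as inclusive, exactly two scores fall in two classes: 65 (moderate and marked) and 80 (marked and severe). The score 95 is unambiguous, because the top band starts above it.

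**The case against.** The strongest reply is that the 4 may be a one-character misprint in a condensed article. The form is attached as Additional file 3. If it prints 3 and staff score from the form, no patient's total is affected. Nor does the document state an intended code or maximum, or say that the cut-offs were set for a 0–144 scale. This reply stands, and for that reason the consequence can only be stated conditionally. It does not remove the inconsistency in the printed rule.

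A reader might infer more than the document supports:

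- *That totals are inflated and patients misclassified.* This needs both the printed 4 to be used and 3 to be intended. Neither is shown. Even then, only patients with at least one Severe fear answer are affected, and only those close enough to a cut-off change class.
- *That the shared end points also cause misclassification.* They change no total. They leave the class undefined at two scores.
- *That the group comparison is distorted.* The same code applies to both groups, so it creates no difference by itself. It gives extra weight to Severe fear where the groups already differ.
- *That a class below 55 is missing.* The labels simply start at moderate, so lower scores lie below the lowest labelled band.
- *That the plan should be told to analyse the total as a continuous score.* Section 2.12 already provides means or medians and a t-test or nonparametric test for measurement data. The article does not say that this scale will be analysed by class.

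**Conclusion.** The point holds in a limited, conditional form. The printed fear code is inconsistent with the avoidance code beside it. If it is applied and 3 was intended, the surplus is one point per Severe fear answer: 0 to 24 per patient, with a maximum of 168 instead of 144. Against fixed cut-offs, a single such answer can change a class at 54 or 95. Independently of the code, 65 and 80 have no defined class.

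The size rests on the two assumptions listed with the inputs. The second is an inference from the parallel question, which only Additional file 3 can settle. The outcome is not primary. The text should still be corrected, because it is a stated scoring rule for part of the trial's aim and the correction is simple.

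**What to change.** 1. Check the fear code against the form in Additional file 3. If the form confirms it, correct Severe to 3 in section 2.10.5.
2. In that case, recode any stored fear answer of 4 to 3 before totals are computed. No information is lost, because the printed fear code has no 3. If some records already hold 3 for Severe, the recode also makes the data uniform.
3. Make the bands mutually exclusive by assigning 65 and 80 to one class each, following the source of the cut-offs, and state the choice. The document does not say which side they belong to.

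The cost is a short text correction and one recode, with no new data and no extra patient contact. Section 4.1 reports the study as being in follow-up, so this can be settled before the scale is scored; any totals already computed would need only to be recalculated.

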### Follow-up

2.11

After finishing the interventions of 2 weeks, telephone follow-up will be done on all patients for 1 year. We follow these patients on a monthly basis. If the patients were died, we will terminate our follow-up.

### Statistical analysis

2.12

Statisticians from coordination center will oversee this work. We analysis all data sets by IBM SPSS Statistics 24.0 software. We express collected data by mean ± standard deviation or median and interquartile distance. The comparison between groups of measurement data which accorded with normal distribution and homogeneous variance is *t*-test. At the same time, the nonparametric test is used for non-compliance with a normal distribution. Chi-Squared test will be used to compare the count data or rate, and the logistic test to compare the survival rate between groups. P value <.05 is considered as statistically significant.

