#### Second outcomes

2.10.2

1.Vital signs (d1-14), temperature, heart rate, blood pressure, respiratory rate (RR), oxygen saturation.2.Chest computed tomography (CT) score (d1, d7, d14), in our study we use high resolution computed tomography (HRCT). According to the existing scoring standards,^[22,23]^ each lobe will be graded. 0 points = no pathological changes of lung lobe, 1 point = pathological changes in 0% to 25% of lung lobes, 2 points = pathological changes in 25% to 50% of lung lobes, 3 points = pathological changes in 50% to 75% of lung lobes, 4 points = pathological changes in 75% to 100% of lung lobes, the total score of 5 lobes is used as the chest CT lesion score of each patient. We compare the mean value of lung CT scores.3.Inflammatory index (d1, d3, d5, d7, d14): peripheral hemogram (the count of peripheral blood leukocyte and lymphocyte), C-reactive protein (CRP), procalcitonin (PCT), tumor necrosis factor (TNF-a), interleukin-6 (IL-6), interleukin-10 (IL-10).4.Main organ function (d1, d3, d5, d7, d14): alanine aminotransferase (ALT), aspartate aminotransferase (AST), total serum bilirubin (STB), blood urea nitrogen (BUN), serum creatinine (Cr).5.Coagulation index (d0, d7, d14): blood platelet count (PLT), D-dimer, activated partial thromboplastin time (APTT), prothrombin time (PT), fibrinogen (Fg).6.Acute Physiology and Chronic Health Evaluation (d1, d3, d5, d7, d14, APACHE-II, Additional file 2) score: we compare the mean value of APECHA II the scores between 2 groups, and calculate improvement rate in APECHA II score = (d14 scored-0 score)/d0 score.

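### Repeated laboratory, CT and APACHE II outcomes get unadjusted two-group tests in a non-randomised cohort, so a baseline difference in severity can carry into the later comparisons

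*Protocol article*

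**What the plan says.** Section 2.12 (Statistical analysis) of the protocol article gives one rule for continuous data: "The comparison between groups of measurement data which accorded with normal distribution and homogeneous variance is" a t-test, and "the nonparametric test is used for non-compliance with a normal distribution". The threshold is general: "P value <.05 is considered as statistically significant". The section names no covariate, no repeated-measures model and no rule for multiple tests.

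Section 2.10.2 (Second outcomes) lists the repeated outcomes and their days:

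- "Inflammatory index (d1, d3, d5, d7, d14"), seven markers
- "Main organ function (d1, d3, d5, d7, d14"), five markers
- "Coagulation index (d0, d7, d14"), five markers
- "Chest computed tomography (CT) score (d1, d7, d14"), one score, with the comparison stated as "We compare the mean value of lung CT scores"
- APACHE II on D1, D3, D5, D7 and D14, compared by group means and also by an improvement rate, which is the D14 score minus the d0 score, divided by the d0 score.

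Section 2.8 (Grouping) forms the groups by whether the patient uses the granule, 1:1, and pairs them on sex, age and underlying disease. The Discussion lists the absence of randomisation as a limitation.

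**The concern.** Pairing on three background factors does not balance how ill patients are at entry. No laboratory value, CT score or APACHE II score is a pairing factor. If users and non-users of the granule differ on D1, a raw comparison of later means contains part of that difference, and nothing in the stated analysis takes it out.

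The aims depend on these outcomes. The Introduction wants to follow changes over time and to reveal a possible immune mechanism, and the Discussion returns to changes in the indicators. A comparison of group means at a visit does not estimate within-patient change, and it leaves unused a baseline value that the schedule already collects. At stake is whether an initial difference in severity gets reported as efficacy or as mechanism. Having many secondary comparisons at one unadjusted threshold adds some chance findings, but this is the lesser issue.

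**Working it through.** **Inputs from the article.** Section 2.7 gives 300 patients (4 centres × 75 = 300), states that no sample size could be calculated, and supposes 10% withdrawal. So 300 × 0.9 = 270, or 135 per group. The plan gives no error rate beyond P<.05 per test, so there is no further figure to reproduce. Two-sided tests are assumed.

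**Assumed inputs (not in the article).** d is a systematic baseline difference between groups in SD units, taken from 0 to 0.5. r is the correlation between the baseline and later value of the same variable, taken from 0.3 to 0.7. The granule is assumed to have no effect, the groups are treated as independent samples, the SD is equal at both visits, and there is no confounding beyond the baseline value.

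**1. Baseline difference carried forward.** The later means differ by d × r SD. The standard error is √(2/135) = 0.122 SD. With m = d × r / 0.122, the rejection rate is 1 − Φ(1.96 − m) + Φ(−1.96 − m).

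| d (SD) | r = 0.3 | r = 0.5 | r = 0.7 |
|---|---|---|---|
| 0 | 5% | 5% | 5% |
| 0.1 | 5.7% | 7.0% | 8.9% |
| 0.2 | 7.8% | 13.0% | 21.0% |
| 0.3 | 11.5% | 23.4% | 40.7% |
| 0.5 | 23.4% | 53.8% | 82.0% |

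For example, d = 0.2 and r = 0.5 gives a shift of 0.10 SD, m = 0.82 and a rejection rate of 13.0%.

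**2. What adjustment does.** Under the same assumptions, conditioning on the baseline value removes the shift. It also cuts the residual variance to 1 − r², which is 0.91, 0.75 and 0.51 for r = 0.3, 0.5 and 0.7.

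**3. Number of comparisons.** Post-baseline visits as listed in Section 2.10.2:

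- inflammatory 7 × 4 = 28
- organ function 5 × 4 = 20
- coagulation 5 × 2 = 10
- CT 1 × 2 = 2
- APACHE II means 1 × 4 = 4

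The total is 28 + 20 + 10 + 2 + 4 = 64. Expected false positives under no effect and no imbalance are 64 × 0.05 = 3.2. The improvement rate makes it 65 (3.25). Coagulation at the Table 1 visits instead makes it 74 (3.7).

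At D14 only there are 17 laboratory variables + CT + APACHE II = 19 comparisons, and 19 × 0.05 = 0.95.

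Correlation between tests leaves the expectation at 3.2 but widens the spread. Independent tests give a 96% chance of at least one false positive and 63% of at least three. In simulation, assumed correlations of 0.5 within and 0.1 between outcomes give 93% and 56%; 0.8 and 0.5 give 63% and 32%.

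**The case against.** The strongest reply has four parts.

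- **Baseline is used once.** A reader might infer that baseline is ignored throughout. It is not: the APACHE II improvement rate is relative to baseline. That stands, but it covers one comparison, and dividing by the baseline score is not an adjustment for it. It also cites a d0 score, although APACHE II is scheduled from D1.
- **No imbalance is shown.** A reader might infer that the comparisons are biased. The article does not support that as a fact. It pairs the groups, acknowledges the lack of randomisation and reports no baseline data. The bias is conditional, and its size rests on assumed values of d and r. What remains is that the pairing factors include no measure of initial severity on these outcomes.
- **Testing at every visit is not stated.** A reader might infer about 100 tests and several certain false positives. Section 2.10.2 lists measurement days, not tests. Larger counts also need the vital signs and comparisons on D1, which the article does not say it will test. The range of about 1 to about 3 expected false positives is what the text supports.
- **Some of this belongs in an analysis plan.** Multiplicity rules for secondary outcomes, how normality is judged, and the test for normal data with unequal variances are commonly left there, and no such plan is shown. That is accepted, and those points are not pressed. The core differs, because Section 2.12 does state a method, and that method suits this design badly.

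**Conclusion.** The point holds in conditional form. As written, Section 2.12 lets any baseline difference in these outcomes pass into the later comparisons, in a cohort grouped by use of the granule and not paired on severity. If the groups do not differ at baseline, the false-positive rate per test stays at 5%. With 135 per group, a 0.2 SD imbalance takes it to about 13–21% for correlations of 0.5 to 0.7, and 0.5 SD with correlation 0.5 takes it to about 54%. These figures are illustrations under assumed inputs, not estimates for this trial. About 3 further false positives are expected by chance if all 64 post-baseline comparisons are made, and about 1 if only the 19 at D14 are.

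The outcomes are secondary, so the primary result is not at issue. They do carry the mechanistic aim, and the change should be made before analysis.

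**What to change.** In Section 2.12, replace the unadjusted tests of the laboratory, CT and APACHE II outcomes with a baseline-adjusted comparison. Suggested content:

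- Use either analysis of covariance at D14 or one repeated-measures model per variable on the post-baseline visits. Include the baseline value of the same variable, the pairing factors and centre; the repeated-measures model also needs visit and group-by-visit.
- Name D14 as the main contrast, and analyse skewed markers on the log scale.
- Report these secondary outcomes as estimates with 95% confidence intervals, labelled exploratory.
- State which day is the baseline and reconcile the sections: coagulation and the APACHE II improvement rate cite d0, while Table 1 starts at D1.
- Say in the report that the adjustment covers measured baseline differences only and does not remove other confounding. Adjustment by itself does not control multiplicity either, hence the exploratory label.

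The cost is wording and slightly more programming. No new data are needed, since the baseline values are already in the schedule. The article says the trial is in follow-up, so the analysis is the part that can still be changed. The downside is that fewer results can be called significant.
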